## **11. Reportable Events**

The following incidents will be considered reportable events and will be reported to the CTCC within 24 hours of the event, or the Site Investigator's knowledge of the event.

- Initiation of PD medication
- Change of clinical diagnosis (includes phenoconversion to PD for Prodromal, Genetic Cohort-unaffected and Registry-unaffected subjects)
- Participation in any other clinical trial or study
- Premature withdrawal (e.g. withdrawal of consent)
- Serious Adverse Event (occurring in the appropriate AE follow up window)
- Pregnancy (reported by female subject or female partner of a male subject)
- Death

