#### **4.2.9. Inclusion criteria (Genetic Cohort – PD Subjects)**

- 4.2.9.1. Patients must have at least two of the following: resting tremor, bradykinesia, rigidity (must have either resting tremor or bradykinesia); OR either asymmetric resting tremor or asymmetric bradykinesia
- 4.2.9.2. Parkinson disease diagnosis for 7 years or less at Screening
- 4.2.9.3. Hoehn and Yahr stage less than 4 at Baseline.
- 4.2.9.4. Male or female age 18 years or older at baseline.
- 4.2.9.5. Confirmation of causative LRRK2, GBA or SNCA mutation (willingness to undergo genetic testing as part of the prescreening or documentation of prior genetic testing results).
- 4.2.9.6. Ability to provide written informed consent in accordance with Good Clinical Practice (GCP), International Conference on Harmonization (ICH), and local regulations.
- 4.2.9.7. Willing and able to comply with scheduled visits, required study procedures and laboratory tests.
- 4.2.9.8. For subjects taking any of the following drugs (Neuroleptics, metoclopramide, alpha methyl dopa, methylphenidate, reserpine, or amphetamine derivative) must be willing and medically able to hold the medication for at least 5 half-lives before DaTSCANTM imaging.
- 4.2.9.9. Women who are pregnant or lactating will not undergo DaTSCANTM and/or F-AV-133 imaging assessments. (The imaging assessments that would have occurred during this time will be waived)

- Includes a negative urine (or serum if required by site) pregnancy test on day of Screening scan prior to injection (DaTSCANTM and/or F-AV-133).
  - Includes a negative serum pregnancy test prior to Screening scan injection (F-AV-133 only).
- 4.2.9.10. Women participating in VMAT-2 PET imaging must be of non-childbearing potential **or** be using a highly effective method of birth control 14 days prior to until at least 24 hours after injection of F-AV-133).
- Non-child bearing potential is defined as a female that must be either postmenopausal (no menses for at least 12 months prior to Screening) or surgically sterile (bilateral tubal ligation, bilateral oophorectomy or hysterectomy).

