## 11. Safety/Adverse Events

Site investigators and coordinators will be instructed to assess for adverse events at in-person study visits when an LP, skin biopsy and/or dopamine transporter SPECT imaging activity is conducted, as well as by telephone 7 to 10 days following such activity.

In addition, for select sites, adverse events will be assessed at the in-person visit when [F] AV-133 or [F] florbetaben PET imaging is conducted, by telephone 48 (± 24) hours following such activity. Each subject must be carefully monitored for adverse events (AEs). An assessment must be made of the seriousness, intensity, and relationship to the study procedure (LP or skin biopsy) and/or administration of the study drug (DaTSCAN™, [F] AV-133, and/or [F] florbetaben as applicable).

Table 1. Adverse event monitoring timelines:

| Procedure                              | Assessed through visit | 48 hours (+/-24 hrs) telephone contact | 7 to 10 day telephone contact |
|----------------------------------------|------------------------|----------------------------------------|-------------------------------|
| Lumbar Puncture                        | X                      |                                        | X                             |
| Dopamine Transporter SPECT Imaging     | X                      |                                        | X                             |
| AV-133 PET Imaging                     | X                      | X                                      |                               |
| [  F] florbetaben Imaging | X                      |                                        | X                             |
| Skin biopsy                            | X                      |                                        | X                             |

Events occurring outside of the study drug/ study procedure AE reporting period do not have to be recorded for study purposes (i.e., they do not have to be captured on the AE log).

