### 10.1 Adverse Event Definitions

#### Adverse Events (AE)

An AE is any undesirable experience occurring to a subject during a clinical trial, whether or not considered related to the investigational product.

Pre-existing conditions (i.e., undesirable experiences, signs or symptoms that begin prior to the Screening Visit) will be recorded on the medical history CRF page. These conditions will not be reported as an AE unless they worsen in intensity or frequency after the Screening Visit (per the reporting period defined in section 9 above).

Treatment-emergent AEs are undesirable experiences, signs, or symptoms that begin or worsen in intensity or frequency at the time of or after the administration of study drug (per the reporting period defined in section 9 above).

For reporting purposes, Avid (manufacturer of [F] AV-133) will distinguish among pre-existing conditions and treatment-emergent AEs.

*Serious Adverse Event (SAE)*

An SAE is an AE that is fatal or life-threatening, or results in hospitalization, prolongation of hospitalization, persistent or significant disability/incapacity, or a congenital anomaly/birth defect. A life-threatening AE is an AE that, in the view of the investigator, places the subject at immediate risk of death from the reaction, as it occurred. Important medical events that may not result in death, be life-threatening, or require hospitalization may be considered an SAE when, based upon appropriate medical judgment, they may jeopardize the subject and may require medical or surgical intervention to prevent one of the outcomes listed in this definition.

Inpatient admission in the absence of a precipitating, treatment-emergent, clinical adverse event is not subject to immediate reporting. For example:

- Admission for treatment of a pre-existing condition not associated with the development of a new adverse event
- Social admission (e.g., subject has no place to sleep)
- Protocol-specific admission during a clinical study (e.g., for a procedure required by another study protocol)
- Optional admission not associated with a precipitating clinical adverse event (e.g., for elective cosmetic surgery)

Inpatient admission does not include the following:

- Emergency Room/Accident and Emergency/Casualty Department visits
- Outpatient/same-day/ambulatory procedures
- Observation/short-stay units
- Rehabilitation facilities
- Hospice facilities
- Respite care (e.g., caregiver relief)
- Skilled nursing facilities

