### **13.6 Unknown Risks**

In addition to the known risks listed above, the imaging procedures in this study may cause unknown risks to the participant, or a developing embryo or fetus or possible risks to the future offspring of male participants. Female subjects or a female partner of a male subject who report a pregnancy within 30 days of DaTSCAN™ injection will be asked to have a urine pregnancy test.

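### A subject's pregnancy after DaTSCAN is reportable but its outcome is not asked for, and a birth defect would practically always miss the windowed SAE item

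*Protocol*

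**What the plan says.** Two protocol sections carry the number 11; they are named here by title.

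- **Reportable Events** requires notice to the CTCC within 24 hours of "Pregnancy (reported by female subject or female partner of a male subject". No time limit and no outcome is attached. The serious-event item in the same list is limited: "Serious Adverse Event (occurring in the appropriate AE follow up window".
- **Safety/Adverse Events** sets that window. For DaTSCAN it is the visit plus a call at 7 to 10 days (Table 1 and 6.3.1). It adds: "Events occurring outside of the study drug/ study procedure AE reporting period do not have to be recorded for study purposes".
- **10.1** includes among serious outcomes "persistent or significant disability/incapacity, or a congenital anomaly/birth defect".
- **10.4** stops follow-up of an ongoing event 30 days after the last injection or lumbar puncture.
- **10.5** asks the investigator to telephone within 24 hours of learning of a serious event, and gives no onset window.
- **13.6** accepts unknown risk to "a developing embryo or fetus or possible risks to the future offspring of male participants". Its only action is that women "who report a pregnancy within 30 days of" a DaTSCAN "injection will be asked to have a urine pregnancy test".
- **4.2.9.9 and 4.2.11.7** (Genetic Cohort) do not bar pregnancy; pregnant women skip the scan: "The imaging assessments that would have occurred during this time will be waived". The contraception rule in 4.2.9.10 and 4.2.11.8 applies to VMAT-2 PET only. In contrast, 4.2.1.9, 4.2.3.4 and 4.2.7.5 exclude pregnancy, or planning one, in the PD, Healthy Control and Prodromal cohorts.

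**The concern.** The protocol names a fetal risk, lists a birth defect as a serious event and requires notice of the pregnancy. It then applies to that event a window built for reactions to an injection or a lumbar puncture. A birth defect cannot show itself on that timescale. Followed to the letter, the study learns that an exposed pregnancy occurred, may confirm it with a urine test, and has no duty to find out how it ended.

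At stake is the completeness of the DaTSCAN safety data that the Clinical Study Oversight Committee reviews under Section 18. With so few cases likely, each missing outcome removes most of what could be learned. No estimate of progression and no study objective is affected.

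**Working it through.** The protocol gives no figure here to reproduce. The check compares its time limits with the time a pregnancy takes.

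**Inputs from the protocol**

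- AE window after DaTSCAN: at most 10 days (Safety/Adverse Events, Table 1).
- Cap on follow-up of an ongoing event: 30 days (10.4).
- Urine-test step: pregnancy reported within 30 days of injection (13.6).
- Genetic Cohort scans: screening (up to 45 days before baseline), Month 24 and Month 48. No lumbar puncture at Month 6 (5.3.6). Calls at Months 27, 33, 51 and 57; visits at Months 30, 36, 54 and 60.

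**Assumptions, not in the protocol**

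- 266 days from conception to term; earliest viable birth 154 days after conception.
- Conception between 10 days before injection (test still negative) and 30 days after.
- 30.44 days per month.

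**Step 1: day of birth = day of conception relative to injection + gestation**

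- Conception on day 0, term: 0 + 266 = 266.
- Conception on day 30, term: 30 + 266 = 296.
- Conception 10 days before, earliest viable birth: −10 + 154 = 144.

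Even the earliest case, day 144, is far beyond 10 days and beyond the 30-day cap.

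**Step 2: could a later procedure's window catch the birth?**

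| Scan | Term birth (study month) | Next scheduled procedure window opens |
|---|---|---|
| Screening | −45/30.44 + 266/30.44 = 7.3, to 296/30.44 = 9.7 | Month 12: 12 − 30/30.44 = 11.0 |
| Month 24 | 24 + 266/30.44 = 32.7, to 24 + 296/30.44 = 33.7 | Month 36: 36 − 30/30.44 = 35.0 |
| Month 48 | 48 + 266/30.44 = 56.7, to 48 + 296/30.44 = 57.7 | Month 60: 60 − 30/30.44 = 59.0 |

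The baseline lumbar puncture after a screening scan does not help: its window closes by about day 45 + 10 = 55, before day 144. Only an optional companion procedure that happened to fall at the right time could overlap.

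**Step 3: when would a pregnancy first be mentioned?** After the 7-to-10-day call, the next routine contact following a Month 24 or 48 scan is 3 × 30.44 = 91 days after it. A pregnancy first mentioned then is reportable, but it is past the 30-day limit for the urine test, so no written step follows.

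**Step 4: do existing contacts reach the outcome?** After a Month 24 or 48 scan, contacts fall at 3, 6, 9 and 12 months: 91, 183, 274 and 365 days. If the scan is 30 days late and the next annual visit 30 days early, the last is at 365 − 60 = 305 days, still after day 296. After a screening scan, the Month 6 visit falls at 183 to 183 + 45 = 228 days and the Month 12 visit at 365 to 410 days; with the visit 30 days early, the latter is no sooner than 335 days.

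**The case against.** **Exposure is very rare.** This stands. 6.3.1.1 requires a pregnancy test confirmed negative before injection, which rules out an established pregnancy. Section 1.2 puts LRRK2 and GBA disease at around or after 60. SNCA disease typically starts in the 40s, but few families are known. Unaffected carriers must be at least 45, or 30 for SNCA (4.2.11). Genetic Cohort PD subjects may enrol from 18 (4.2.9.4), but few women of childbearing age can be expected. What remains is very early pregnancy missed by the test, or conception soon after the scan.

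**A route for a known defect already exists.** This also stands. 10.5 has no onset window, the sentence on out-of-window events permits non-recording and does not forbid reporting, and local ethics and Radiation Safety Committee rules apply. A reader might infer that 10.5 contradicts Reportable Events or that a late report is barred; the text supports neither. But 10.5 starts only when the investigator becomes aware, and nobody is told to ask.

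**Procedures may sit elsewhere.** 15.1 refers undescribed procedures to Operation Manuals, which are not shown, and companion protocols may cover AV-133 and florbetaben. The point is therefore limited to DaTSCAN and to this text. It is still more than an omission, because the window is written here and excludes the event as written.

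**Partners of male subjects.** A reader might infer that a defect in a partner's child is likewise a missed SAE. The protocol does not support that: 10.1 defines an adverse event as one that happens to a subject, and the partner is not enrolled. Her pregnancy is reportable, but the child's condition is not plainly an SAE of the study.

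**Tracer dose.** 13.4 expects no pharmacological or toxicological effect. This supports low weight, though 13.6 still lists the fetal risk as unknown.

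**Conclusion.** The point holds for female subjects, mainly in the Genetic Cohort. The protocol requires notice of a pregnancy but not its outcome, and a congenital anomaly that 10.1 treats as serious would practically always fall outside the SAE item in Reportable Events. The conclusion rests on the 10-day window and on births no earlier than about day 144 after injection; no plausible change in the gestation assumptions alters it.

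It is minor. No case count can be derived from the protocol, exposure should be very rare, a known defect can already be reported, and no objective depends on it. It should not be read as saying that the protocol ignores pregnancy: it tests before injection, suspends scans and requires notice without a time limit.

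**What to change.** In Reportable Events, state two things for a DaTSCAN-exposed pregnancy in a subject, meaning one present at the injection or conceived within 30 days after it:

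1. A congenital anomaly is reportable as a serious adverse event regardless of the AE window.
2. The outcome is recorded at visits or calls already scheduled, until it is known or the subject leaves the study.

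Follow a partner's pregnancy only with her agreement.

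The cost is amendment wording and one more item on the pregnancy report. Routine Genetic Cohort contacts after screening, Month 24 and Month 48 scans already reach past the expected date of birth. After Month 60 a phone visit or annual visit continues every 6 months while the subject stays in the study (5.3.21). Outcomes may be missed in subjects who withdraw, including those scanned at the withdrawal visit, and in those scanned close to the end of their follow-up.

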## **12. Referrals**

If a research assessment, lab or MRI result reveals a clinically significant abnormality (e.g., indication of suicidality, depression, or renal impairment on metabolic profile) the subject should be informed of this result and instructed to follow up with his or her primary care physician. Should there be a safety concern warranting a referral for medical or psychiatric follow-up, the Investigator should provide the subject with the appropriate referral as necessary.

## **13. Potential Risks**

### **13.1 Blood Sampling**

Risks associated with venous blood draw include pain and bruising at the site where the blood is taken. Sometimes people can feel lightheaded or even faint after having blood drawn.

### **13.2. Lumbar Puncture**

The most common risks of a lumbar puncture are pain at the site and a temporary headache usually due to a small amount of CSF leakage around the needle insertion site. Lying down for a few hours after the test can make a headache less likely to occur. There is a slight risk of infection because the needle breaks the skin's surface, providing a possible portal of entry for bacteria. A temporary numbness to the legs or lower back pain may be experienced. There is a small risk of bleeding in the spinal canal. Subjects will have blood drawn at Screening to test for coagulopathies.

### **13.3. MRI / DTI**

Subjects should notify the study doctor if they suffer from claustrophobia because they may become anxious while in the magnetic resonance scanner. There may be loud noises such as knocking or hammering that occur while the MRI is being conducted. Subjects should also inform the study doctor if they have a pacemaker or metal implants (screws, plates or clips) because this may preclude MR evaluation.

### **13.4. Imaging**

Specific potential risks for dopamine transporter SPECT imaging and VMAT-2 PET imaging are as follows:

- 1) radiation exposure from DaTSCAN™, F-AV-133, or [I]β-CIT, the Co transmission source, and from Co containing markers,
- 2) potential pharmacological effects of DaTSCAN™,
- 3) having an intravenous injection.

Risks of DaTSCAN™: DaTSCAN™ is administered at radiotracer doses and is not expected to have any pharmacological or toxicological effects. DaTSCAN™ binds to the dopamine and serotonin transporter. At pharmacologic doses DaTSCAN™ might be expected to have stimulant-like effects and affect cardiovascular responses. However, in the proposed study the estimated mass dose of DaTSCAN™ is very low - <30/pmol kg. More than 180,000 doses of the drug have been administered to human subjects.

Risks of [F] AV-133: Refer to F-AV-133-PPMI companion protocol Section 6.

Risks of [F] florbetaben: Refer to [F] florbetaben-PPMI companion protocol Section 2.3.

Risks of [I]β-CIT: The U.S. Food and Drug Administration (FDA) has established guidelines for the radiation dose considered acceptable for determining the distribution of radiotracer compounds in normal adult research subjects. The radiation exposure from this study is within the limits specified by the FDA. [I]β-CIT has been given to over 2000 subjects. In a few subjects (less than 1%) minor headaches and metallic taste in the mouth have occurred. It is possible that unexpected side effects could develop.

Iodine: Prior to each injection subjects will be pretreated with Lugol's solution, 10 drops of a saturated solution of potassium iodide) to reduce thyroid uptake of the radioactive agent. Subjects may experience a metallic or bitter taste in their mouths from the iodine. Subjects with allergies to iodine might get itching, a rash, bloating, severe blood pressure changes (shock), and death if given iodine. Subjects who are allergic to iodine will be administered potassium perchlorate rather than Lugol's.

### **13.5 . Risk of Disclosure of Genetic Information**

All genetic information will be maintained in a confidential research file. While every effort will be made to maintain confidentiality there is a small risk that information will be disclosed. A Federal law, called **the Genetic Information Nondiscrimination Act (GINA)** generally makes it illegal for health insurance companies, group health plans and most employers to discriminate based on genetic information. This law generally provides that

- Health insurance companies and group health plans may not request an individual's genetic information from this research.

- Health insurance companies and group health plans may not use genetic information when making decisions regarding eligibility or premiums.
- Employers with 15 or more employees may not use genetic information from this research when making a decision to hire, promote, or fire an individual or when setting the terms of an individual's employment.

However, this law does not protect the subject from genetic discrimination by companies that sell life insurance, disability insurance, or long-term care insurance.

### **13.6 Unknown Risks**

In addition to the known risks listed above, the imaging procedures in this study may cause unknown risks to the participant, or a developing embryo or fetus or possible risks to the future offspring of male participants. Female subjects or a female partner of a male subject who report a pregnancy within 30 days of DaTSCAN™ injection will be asked to have a urine pregnancy test.

### **13.7 Genetic Testing**

There is a small risk of laboratory error with the genetic tests performed as a part of the pre-screening for participation in the Genetic Cohort and Genetic Registry. There is also a risk that the test may not work and will need to be repeated. In some cases where testing needs to be repeated, a new sample may need to be acquired. Up to two samples (blood or saliva) for DNA analysis will be collected from each subject. Either one or both samples may be used for quality control/quality assurance of the testing process to guard against such a risk.

**13.8 Risks of gait and mobility assessments:** Refer to *Characterization of Motor Function and Potential Transition States to Parkinson's Disease in LRRK2 mutation Carriers and Controls* companion protocol.

**13.9 Refer to Passive monitoring of individuals through wearable sensors or non-invasive methods (Sensor-PPMI sub-study)** protocol for risks associated with that companion study.

## **14. Statistical Methods**

### **14.1 Statistical Design**

PPMI is a longitudinal, multi-center study to assess progression of clinical features and imaging and biomic biomarkers in Parkinson disease patients and healthy controls. PD, Prodromal (including the Prodromal and Unaffected Genetic Cohort) and control subjects will be evaluated longitudinally for at least 36 months.

### **14.2 Primary Objective**

To estimate the mean rates of change and the variability around the mean of clinical, imaging and biomic outcomes in early PD patients, and where appropriate to compare these rates between various subsets (including, but not limited to: early PD subjects vs. healthy subjects, PD vs. SWEDD, PD vs. Prodromal, PD with and without LRRK2, GBA or SNCA mutation, unaffected LRRK2, GBA or SNCA mutation carriers vs. healthy subjects) at study intervals ranging from 3 months to 36 months.

### 14.3 Secondary Objectives

- 14.3.1 Comparison between the rates of change in the mean of clinical, imaging and biomic outcomes in various subsets (including, but not limited to: early PD patients and vs. healthy subjects, PD vs. SWEDD, PD vs. Prodromal, PD with and without LRRK2, GBA or SNCA mutation, unaffected LRRK2, GBA or SNCA mutation carriers vs. healthy subjects) at study intervals ranging from 3 months to 156 months.
- 14.3.1. To determine the prevalence of measures of clinical, imaging and biomic outcomes in various subsets (including, but not limited to: early PD patients vs. healthy subjects PD vs. SWEDD, PD vs. Prodromal, PD with and without LRRK2, GBA or SNCA mutation, unaffected LRRK2, GBA or SNCA mutation carriers vs. healthy subjects) at study intervals ranging from baseline to 156 months.
- 14.3.2. To establish the predictive value of early clinical non-motor features, baseline imaging and biomic outcomes for future course of disease.
- 14.3.3. To examine the proportion of SWEDD subjects that have a change in their clinical management at 24 months (SWEDD Clinical Diagnosis and Management Questionnaire).
- 14.3.4. To examine the proportion of Prodromal subjects with one or more risk characteristics [hyposmia (<10th percentile by age and gender), RBD, or LRRK2, GBA or SNCA mutation, and baseline DaTSCAN binding showing minimal to moderate DAT deficit who phenoconvert within two years. To correlate the baseline DaTSCAN binding with risk of phenoconversion
- 14.3.5. To conduct exploratory analyses to examine whether the baseline DaTSCAN binding or progression of clinical, imaging, or biospecimen biomarkers will predict those subjects likely to phenoconvert.
- 14.3.6. Exploratory analysis of SWEDD subjects with substantial evidence of PD followed for longer than 2 years compared to PD subjects

